# Effect of Dual Bronchodilation on the Exercise Capacity of Individuals With Non-Cystic Fibrosis Bronchiectasis: Protocol for a Randomized Controlled Double-Blind Crossover Study

**DOI:** 10.2196/68582

**Published:** 2025-07-28

**Keywords:** bronchiectasis, bronchodilator agents, exercise test, exercise, non-cystic fibrosis bronchiectasis, exercise capacity, thoracoabdominal kinematics

## Abstract

**Background:**

Bronchodilators (BDs) have been used therapeutically to improve exercise capacity in patients with other chronic respiratory diseases. However, the effect of BDs on the exercise capacity of individuals with non-cystic fibrosis bronchiectasis (NCFB) is poorly understood.

**Objective:**

The aim of this study was to evaluate the effects of BDs on exercise capacity and thoracoabdominal kinematics in patients with NCFB.

**Methods:**

This crossover randomized controlled trial will involve 45 outpatients with NCFB aged 18 to 59 years. They will be evaluated in 3 visits. On day 1, the maximal exercise capacity (cardiopulmonary exercise test; peak work rate [W_peak_]) will be assessed. On day 2, individuals will be randomized to receive either BD (ipratropium bromide 160 µg and fenoterol hydrobromide 400 µg) or a placebo and then undergo simultaneous endurance exercise capacity (constant work-rate exercise test) and thoracoabdominal kinematics (optoelectronic plethysmography) assessments. After at least 1-week washout (day 3), the individuals will repeat the same assessments as on day 2 in the reverse order. The time to the limit of tolerance will be obtained in both groups (BD and placebo groups) as the primary outcome. Thoracoabdominal kinematics will be assessed at 3 time points: at rest, during unloaded exercise, and at 75% W_peak_. The total chest wall and compartmental volumes as well as thoracoabdominal asynchrony will be assessed. The assessors and patients will be blinded to the interventions (BDs or placebo). Data will be compared using 1-sided *t* tests or Wilcoxon tests and repeated-measures analysis of variance or Friedman tests. Categorical data will be analyzed using the chi-square test or Fisher test. The associations among variables will be analyzed using Pearson or Spearman correlation. The significance level will be set at 5% (*P*<.05).

**Results:**

The ethics approval was granted in November 2018, and a pilot study was commenced in April 2019 but was interrupted due to the COVID-19 pandemic. The study restarted in April 2022, and data collection is anticipated to continue until November 2025. The publication of the results is anticipated to be in 2025 or 2026.

**Conclusions:**

There is no evidence that BDs can improve the exercise capacity of patients with NCFB. This trial will compare the endurance exercise capacity of the same individual with and without dual bronchodilation. If successful, this study will demonstrate that exercise capacity can be improved with the use of BDs in adults with NCFB.

**Trial Registration:**

ClinicalTrials.gov NCT05183841; https://clinicaltrials.gov/study/NCT05183841

**International Registered Report Identifier (IRRID):**

DERR1-10.2196/68582

## Introduction

Non-cystic fibrosis bronchiectasis (NCFB) is radiologically characterized by permanent dilation of the bronchi and clinically characterized by productive cough and recurrent respiratory infections [1]. NCFB is becoming increasingly prevalent and can affect individuals of any age [2]. The pathophysiological mechanisms include persistent bacterial infections, dysregulated immune responses, impaired mucociliary clearance, and airway obstruction—all of which can cause long-term lung impairment (vicious vortex) [1].

Although the optimal therapy for NCFB remains unknown, various pharmacological strategies have been proven beneficial for improving both the quality of life and clinical outcomes. Anti-inflammatory treatment seems to reduce the volume of secretions and inflammatory markers in the sputum and improve the quality of life [3]. In general, antibiotics effectively reduce the bacterial load in the airways [4]. Although the role of bronchodilators (BDs) in the treatment of NCFB is less clear, BDs appear to improve lung function in some patients [5]. Neither antibiotics nor anti-inflammatories can significantly improve the lung function of individuals with NCFB [6], making BDs a therapeutic alternative.

The use of BDs for other chronic respiratory diseases such as asthma and chronic obstructive pulmonary disease (COPD) is already well established and recommended in their respective guidelines [7,8]. According to the Global Initiative for Chronic Obstructive Lung Disease [8], the use of BDs (long-acting β-2 agonists or muscarinic antagonists) is indicated for individuals with severe disease, symptoms, or exercise limitations, as they reduce airway resistance, promote lung deflation, and enable better alveolar ventilation, both at rest and during exercise, in this population.

Despite the lack of robust studies demonstrating the effectiveness of BD use in the treatment of NCFB, BDs continue to be among the most commonly prescribed medications worldwide for this population [9,10]. A small previous study in adults with clinically stable NCFB revealed that combining inhaled corticosteroids with long-acting β-2 agonists might improve dyspnea and increase the number of cough-free days compared with high-dose inhaled corticosteroids, with no effect on the quality of life, number of hospitalizations, or lung function [11]. Despite being a randomized trial, neither patients nor assessors were blinded, and there was an overall high risk of bias, according to Goyal and Chang [12]. A more recent and larger study [13] evaluated the effects of 6-month tiotropium (long-acting muscarinic antagonists) treatment in 90 clinically stable adults with NCFB. Compared with placebo, tiotropium improved the forced expiratory volume in the first second (FEV1) by 58 mL and the forced vital capacity (FVC) by 78 mL. Nevertheless, there was no difference in the quality of life, chronic cough, exercise capacity, or neutrophil and eosinophil counts in the blood or sputum. Furthermore, it did not reduce the number of exacerbations. To date, there are no studies on the effect of BDs on the exercise capacity of this population.

In individuals with NCFB, airflow limitation and dyspnea are strongly associated with exercise capacity [14]. It seems plausible that BDs may improve the exercise capacity of individuals with NCFB similar to what has been observed in individuals with COPD. Additionally, thoracoabdominal asynchrony (TAA) is very prevalent in individuals with COPD and is associated with exercise limitations [15,16]. In this population, the main effect of BDs is an increase in the basal inspiratory capacity and changes in dynamic hyperinflation during exercise, which improves exercise capacity [17]. However, no study has evaluated TAA or the thoracoabdominal kinematics of individuals with NCFB. Therefore, we hypothesize that dual bronchodilation can improve the exercise capacity of individuals with NCFB and reduce TAA during exercise.

## Methods

### Study Design

This is a randomized, placebo-controlled, double-blind, crossover trial (Figure 1). Participants are assigned in a 1:1 ratio to 2 treatment periods, each lasting 1 hour, with a 1-week washout period between them.

**Figure 1 figure1:**
[figure not shown]
CONSORT (Consolidated Standards of Reporting Trials) diagram showing the flow of participants through each stage of the randomized crossover trial. BD: bronchodilator; CPET: cardiopulmonary exercise test; CWRET: constant work-rate exercise test; OEP: optoelectronic plethysmography.

### Ethical Considerations

Patients will be recruited from an outpatient tertiary clinic specializing in treating patients with NCFB at Hospital das Clínicas, Universidade de São Paulo, São Paulo-Brazil. The Hospital Research Ethics Committee of the University of São Paulo approved the study (approval 3.008.886). All participants will provide written informed consent prior to data collection. The data will be deidentified by excluding the main identifying elements such as name, address, date of birth, phone number, email, medical record number, institutional identification number, and social security number. Participants will receive an identification code, according to the order of inclusion in the study. The participants will be informed about the possibility of withdrawing at any time, without loss of their treatment at the institution. Additionally, the participant will be informed about the voluntary nature of their participation. Financial assistance for transportation will be available. This study is registered on ClinicalTrials.gov as NCT05183841.

### Eligibility Criteria

Individuals aged 18-59 years, of either sex, diagnosed with NCFB on the basis of features on the computed tomography scan of the thorax [18], clinically stable (last 30 days without exacerbation/hospitalization), with trapped air on body plethysmography, that is, if residual volume/total lung capacity ratio is higher than 120% of the predicted [19,20], and physically inactive (<60 minutes of structured or planned physical activity per week) [21] will be eligible to participate. The exclusion criteria will be as follows: smokers or former smokers (>10 pack-years); other concomitant respiratory diseases, and cardiovascular or musculoskeletal diseases that may interfere with the patient’s evaluations; uncontrolled arterial hypertension or diabetes; and pregnant or breastfeeding. Patients who have participated in a pulmonary rehabilitation program in the last 6 months or are participating in another research protocol as well as those with cognitive deficits that limit comprehension will also be excluded.

### Experimental Design

Patients will be evaluated on 3 nonconsecutive days. Clinical data (anthropometrical and bronchiectasis severity assessed by FACED [FEV1% predicted score, Age, Chronic colonization by *Pseudomonas aeruginosa*, Radiological extension, Dyspnea]) [10] will be obtained from the participants’ medical records. On day 1, pulmonary function will be assessed via whole-body plethysmography, and the maximal exercise capacity will be measured via a cardiopulmonary exercise test (CPET) to obtain the peak work rate (W_peak_). On day 2, patients will be randomly allocated to receive BDs (160 µg of ipratropium bromide and 400 µg of fenoterol hydrobromide) or a placebo (norflurane or HFA134A, a harmless propellant), followed by simultaneous assessments of endurance exercise capacity (constant work-rate exercise test, CWRET) and thoracoabdominal kinematics (optoelectronic plethysmography). On day 3, after at least 1-week washout with no maximum deadline, the patient will repeat the same assessment as on day 2 in the reverse order. This washout period was defined according to the maximum BD withholding time (48 hours) [22], aiming to minimize the carryover effect. In case of NCFB exacerbation during the washout period, a 30-day recovery interval will be performed for the next assessment. Spirometric evaluations will be performed pre-CWRET before and after BDs or placebo. The time to the limit of tolerance (T_lim_) will be obtained under both conditions (BDs and placebo). Thoracoabdominal kinematics will be assessed at 3 time points: at rest (T1), during the unloaded exercise (T2), and at 75% W_peak_ obtained from CPET (T3). Thoracoabdominal kinematics will assess volume variables, including total chest wall volume, compartmental volume, and TAA. The assessor and patient will be blinded to the intervention (BDs or placebo). All exercise tests will be performed on a cycle ergometer (Figure 2).

**Figure 2 figure2:**
[figure not shown]
Experimental design. Assessment of endurance exercise capacity simultaneously with thoracoabdominal kinematics. OEP: optoelectronic plethysmography; T1: thoracoabdominal kinematics assessment at rest; T2: thoracoabdominal kinematics assessment at unloaded exercise; T3: thoracoabdominal kinematics assessment at 75% Wpeak; Tlim, time to the limit of tolerance; TV: television; Wmax: maximal or peak work rate.

### Pulmonary Function

Spirometry and lung volume measurements will be obtained via a calibrated spirometer (nSpire KoKoUSB Spirometer) and a whole-body plethysmograph (Elite Dx, Elite Series; Medical Graphics Corporation), respectively, according to standardized recommendations [23]. The measurement of the diffusing capacity of the lungs for carbon monoxide will be obtained by the single-breath maneuver in absolute and relative values [24]. The FVC, FEV1, total lung capacity, residual volume, and diffusing capacity of the lungs for carbon monoxide will be expressed as percentages of the predicted values [25-27]. Spirometric evaluations will be performed before CWRET and before and after BDs or placebo, and a change of >10% relative to the predicted value for FEV1 or FVC will be considered a positive response to the BD [24].

### CPET Examination

CPET will be performed using an electrical cycle ergometer (Corival, Lode BV; Medical Technology) linked to a digital system equipped with an exercise evaluation system (CardioO2 System; Medical Graphics Corporation) in accordance with the American Thoracic Society/American College of Chest Physicians guidelines [28]. Peripheral oxygen saturation (SpO_2_), as measured via pulse oximetry (Onyx, Model 9500; Nonin) and electrocardiography (Welch Allyn CardioPerfect, Inc), will be monitored continuously during the tests. The following variables will be recorded breath-by-breath during rest, exercise, and subsequent testing: work rate, oxygen consumption, minute ventilation, carbon dioxide production, respiratory exchange rate, and heart rate. Additionally, blood pressure, SpO_2_, and the modified Borg scores (0-10) for leg discomfort and dyspnea [29] will be measured at rest and every 2 minutes during testing until the end of testing [30]. The participants will perform a ramp symptom-limited CPET consisting of 2 minutes of rest, 2 minutes of warm-up (unloaded pedaling), and an incremental work period (an increase from 10 W/min to 20 W/min, considering the patient’s level of daily activity) [31]. The predicted CPET values will be obtained from the Brazilian population [32]. Although there is no specific information about the threshold at which arterial desaturation becomes hazardous, the test should be terminated if SpO_2_ falls below 80% [33].

### CWRET Analysis

CWRET will be performed using an electrical cycle ergometer after a CPET is completed for an appropriate work rate for CWRET to be estimated [34]. CWRET is selected to be 75%-80% of CPET W_peak_. Continuous monitoring of SpO_2_, heart rate, and modified Borg scores (0-10) for leg discomfort and dyspnea will be performed according to the American Thoracic Society/American College of Chest Physicians guidelines [28]. The target duration for CWRET will be 180 seconds to 480 seconds. For patients not achieving a baseline T_lim_ within 180-480 seconds, the work rate will be adjusted to bring T_lim_ within the desired range (ie, SD 5 W), and the test will be repeated [35].

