### Thoracoabdominal Kinematics

Thoracoabdominal kinematics will be evaluated by optoelectronic plethysmography (BTS), as previously described [36]. Briefly, a video is recorded with 8 solid-state charge-coupled cameras operating at 100 frames per second and synchronized with an infrared flashing light-emitting diode. Four cameras will be positioned in front of the participant and 4 behind; 89 retroreflective markers will be placed on the anterior and posterior sides of the trunk according to a previously described protocol [37]. A 3D calibration of the equipment will be performed on the basis of the manufacturer’s recommendations. The assessment will be performed with the individual on a cycle ergometer at 3 time points, that is, at rest, during the unloaded exercise, and at 75% W_peak_, according to the values obtained from CPET. The data analysis will use an average of 6 homogeneous respiratory cycles.

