### Interventions

Participants will be instructed not to consume alcohol or coffee or perform intense physical activity the day before the exercise test. In addition, they will be oriented to suspend routine BD medication for 6 hours for short-acting β-2 agonists and for 12 hours for short-acting muscarinic antagonists, and for 24 hours for long-acting β-2 agonists and 48 hours for long-acting muscarinic antagonists before the exercise test, according to the European Respiratory Society 2019 guidelines [22]. In case of exacerbation of symptoms during the period of BD suspension, the patient will be advised to use the medication, and the test will be rescheduled.

According to the randomization, a trained respiratory physiotherapist will administer either BD or placebo, ensuring proper treatment timing by using a timer and correct inhaler technique. Missed sessions will be rescheduled according to the participant’s availability to improve patient adherence. The intervention will combine 2 BD compounds: ipratropium (20 µg) and fenoterol (50 µg). Ipratropium is a short-acting antimuscarinic agonist, and fenoterol is a short-acting β-2 agonist BD. The BD or placebo will be delivered to the patient via a pressurized metered-dose inhaler with a spacer at least 20 minutes prior to CWRET, and CWRET will be performed no more than 1 hour after the administration of BD or placebo.

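### The rule that adjusts the CWRET work rate on a baseline T_lim has no test before study drug to act on in the visits described

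*Protocol article*

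**What the plan says.** Experimental Design in the protocol article sets the calendar: "Patients will be evaluated on 3 nonconsecutive days". Day 1 holds lung function and the incremental CPET. Then "On day 2, patients will be randomly allocated to receive BDs" or placebo, "followed by simultaneous assessments of endurance exercise capacity (constant work-rate exercise test, CWRET"). Day 3, at least a week later, repeats day 2 with the other treatment. The section says T_lim is obtained under BD and under placebo, and names no third condition. The Abstract gives the same order.

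CWRET Analysis takes the load from the CPET: "CWRET is selected to be 75%-80% of CPET W_peak". It sets a target duration of 180 to 480 s and adds: "For patients not achieving a baseline T_lim_ within 180-480 seconds, the work rate will be adjusted to bring T_lim_ within the desired range". The adjustment is given in terms of 5 W, and the test is repeated. The word *baseline* is tied to no visit.

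Two other statements bear on this. Thoracoabdominal Kinematics, measured during the same exercise, places its time points "at rest, during the unloaded exercise, and at 75% W_peak_, according to the values obtained from CPET". Interventions asks for at least 20 minutes between dosing and the test, and says that "CWRET will be performed no more than 1 hour after the administration of BD or placebo".

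**The concern.** T_lim is the primary outcome. If the first T_lim a patient produces comes after BD or placebo, a rule that changes the load and repeats the test according to that value selects on the primary outcome. In patients who receive BD first, it also selects on their response to BD. A long time on BD would lead to a different load and a replaced value, and so would a short time on placebo.

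A crossover depends on the two times being comparable within a patient. That fails if the load differs between days. Even with one load on both days, first-day values kept because they fell inside the window are selected on their own measurement error, while those outside are redrawn. The article does not say in terms whether the adjusted load carries to day 3, whether the rule can act again on day 3, or which of two T_lim values is analysed.

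**Working it through.** **1. Rule against schedule.** The rule needs a baseline T_lim. Day 1 offers a CPET, which is incremental and gives no T_lim. Days 2 and 3 offer a CWRET only after inhalation. The first T_lim in the described visits is therefore the day 2 value. With 1:1 allocation, about half of patients have BD on board when it is measured.

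**2. The plan's own figure.** Data Analysis gives a difference of 55.2 s, SD 119.4 s and n = 39 for 80% power. Reading 119.4 as the SD of the paired difference, the noncentrality is 55.2/119.4 × √39 = 2.89. Power is 80.3% with a two-sided 5% paired t test and 88.3% one-sided. So 39 is reproduced (two-sided), and this concern does not change it. The standard error of the mean difference is 119.4/√39 = 19.1 s.

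**3. How often the rule would fire.** Assumptions not in the documents: placebo mean T_lim 270, 330 or 420 s; between-patient SD 100 or 150 s; within-test SD 119.4/√2 = 84.4 s; true effect 55.2 s. With between-patient SD 100, the SD of a first test is √(100² + 84.4²) = 130.9 s. Normal tail areas then give:

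| Placebo mean | First treatment | Above 480 s | Below 180 s | Repeated |
|---|---|---|---|---|
| 270 s | BD (325.2 s) | 11.8% | 13.4% | 25% |
| 270 s | placebo | 5.4% | 24.6% | 30% |
| 420 s | BD (475.2 s) | 48.5% | 1.2% | 50% |
| 420 s | placebo | 32.3% | 3.3% | 36% |

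Over all settings 25% to 53% of first tests are repeated, and the rate depends on treatment.

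**4. Effect on the estimate.** Simulation with at least 200,000 patients per setting. Further assumptions: one repeat; one 5 W step (reading the article's 5 W as a step size) moves T_lim by 60 to 120 s; times cannot fall below a floor (30 s reproduces the figures). The floor is why the first row reaches down to 52 s. Without it that row is 55 s throughout, and the ends of the other ranges move by about 1 s or less.

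| Reading of the rule | Mean BD − placebo | Power at n = 39, two-sided | One-sided |
|---|---|---|---|
| No reset | 52-55 s | 79-81% | 87-89% |
| Day 2 only, new load kept on day 3 | 49-53 s | 76-79% | 85-87% |
| Day 2 only, original load on day 3 | 39-49 s | 44-66% | 57-78% |
| Each period separately | 23-42 s | 26-66% | 37-77% |
| Both periods, changes carried forward | 27-44 s | 34-66% | 46-78% |

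**5. Sequences.** In the second row the average hides a split. At placebo mean 420 s and SD 100 s, the difference is about 35 s in BD-first and 71 s in placebo-first patients. That is an apparent period effect of (71 − 35)/2 = 18 s with no true period effect. BD-first patients are also moved to a heavier load more often: the net proportions are 48.5 − 1.2 = 47.3% against 32.3 − 3.3 = 29.0%. The gap of 18.3 percentage points times 60 to 120 s gives a load-driven difference of 11 to 22 s between sequences on day 3. The planned GEE model for carryover, period and sequence could read these as real.

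**6. Load and timing statements.** The load is a range of 75% to 80% of W_peak in one section and 75% in the kinematics sections, although both describe the same exercise. An adjusted load may match neither. The post-dose window runs from 20 to 60 minutes, so 40 minutes are available. Two tests of up to 480 s take 16 minutes, plus unloaded phases and recovery.

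**The case against.** The strongest reply is that *baseline* ordinarily means before study treatment. The authors may run an untreated CWRET to calibrate the load and simply not list it. Figure 2 is not shown, and the article condenses a fuller protocol. This stands as a possibility: with such a test the bias disappears. What remains is that the stated rule and the stated schedule do not fit each other on the primary endpoint.

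Secondly, Experimental Design has day 3 repeat the same assessment as day 2, which favours one load on both days. This also stands. The average loss is then about 1 to 5 s, small beside a standard error of 19 s. The larger losses need loads that differ between days or a rule that acts in each period. The text does not state either, nor does it rule them out in terms of watts.

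A reader might infer more than the documents support:
- That no untreated test exists. The article shows only that none is described.
- That the rule would manufacture a benefit. In every setting examined the bias runs towards no effect.
- That a repeat is impossible within the post-dose window. Forty minutes is tight once recovery is allowed for, but it is not a contradiction.
- That the sample size is wrong because of this rule. It is not.

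**Conclusion.** The concern holds as a conflict between a stated rule and a stated schedule. In the visits described, the adjust-and-repeat rule can find only a post-dose T_lim, and followed that way it makes retesting depend on the primary outcome and on treatment. This goes beyond detail that an article may leave out, because the two sections give incompatible instructions for the primary measurement.

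The size depends on what the text leaves open: modest on average with diverging sequences if one load is kept on both days, substantial dilution and lost power otherwise, and none if the rule acts on an untreated test. These sizes rest on the assumed T_lim distribution and on the assumed response to a 5 W step, neither of which the documents give. The conflict itself rests on no assumption.

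**What to change.** Reconcile Experimental Design, CWRET Analysis and Thoracoabdominal Kinematics so that they state:
- Each patient's load is set before any study drug is given, from the CPET or from an untreated CWRET if one is already performed. In the latter case, show that test in the schedule.
- The load is one consistently stated percentage of W_peak.
- The identical load is used on days 2 and 3.
- No load is reset after BD or placebo.
- The first post-dose T_lim of each day is analysed, even if it lies outside 180-480 s.

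Results reports 39 consents by May 2025, so much of this concerns data already collected. Before unblinding, list any patients retested after dosing. Where the first tests of both days used the same load, make the first test primary and the retest a sensitivity analysis. Where they did not, write down the handling before unblinding too, and report how many patients it affects.

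The cost is wording and a short record check; the sample size does not change. The downside is that some T_lim values stay outside the target range and add some spread.
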